**Figure 1 F1:**
[figure not shown]
The flow chart of this study.

### Outcome measures

2.5

#### Primary outcome measure

2.5.1

The primary outcome measure will be the definition and classification of nausea and vomiting (NCI-CTC AE4.0) and the MASCC (Multinational Association for Supportive Care in Cancer) Antiemesis Tool (MAT) score, 24 hours and fourth day after chemotherapy, for a third consecutive cisplatin-based chemotherapy cycle. These 2 scales are used to describe the condition and degree of CINV in cancers, and strongly recommended by different international guidelines and widely applied. They are easy-to-use and evaluate the likelihood of a patient's condition. The definition and classification of nausea and vomiting stages the nausea and vomiting into 3 and 4 grades, respectively; and MAT is comprised of 2 sections: 24 hours later and 4 days later. In terms of MAT, each section has 4 identical items including occurrence of nausea and vomiting, frequency of vomiting, and level of nausea.

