## Introduction

1

Chemotherapy-induced nausea and vomiting (CINV) is among the most common and distressing side effects of chemotherapy.^[1]^ It has been shown to significantly affect the quality of life (QoL) and daily function of patients receiving chemotherapy.^[2]^ Moreover, CINV, as a prognostic factor for overall survival, is so severe in some cases that it interrupts the treatment of primary cancer and increases the risk of disease progression,^[3,4]^ which result in treatment-outcome reduction.^[5]^

Cisplatin, which is a cornerstone of chemotherapy for the treatment of multiple cancers, is a highly emetogenic chemotherapy drug.^[6]^ Over 90% cancer patients will vomit within the first 24 hours after the administration of cisplatin-based chemotherapy unless antiemetic drugs are used.^[7]^ Even with the guideline-recommended antiemetic drugs, cisplatin-induced vomiting is controlled in only 60% of patients; therefore, considerable numbers of patients still experience nausea.^[8]^

Although the mechanisms underlying CINV are not clear enough,^[9]^ to date, commonly prescribed medicines,^[10]^ for nausea and vomiting are: 5-hydroxytryptamine-3 serotonin receptor antagonists (5-HT3RA), Neurokinin1 receptor antagonists (NK-1RA), and corticosteroid.^[11]^ However, for all its prominence in CINV management, these drugs are subject to considerably economic burden and side effects, namely insomnia, headaches, dizziness, and constipation.^[12]^ Thus, additional treatments are urgently needed to effectively manage and ameliorate chemotherapy-induced nausea and vomiting (CINV), without those defects in the wake of antiemetic drugs.

An increasing body of evidence points that electroacupuncture (EA) may provide modest benefits in the treatment of CINV.^[13]^ However, the spread of it is surprisingly slow, and EA is still judged as a highly suggestive but not conclusive treatment.^[14–17]^ For certain patients, they are reluctant to accept EA treatment for their intolerance to needling. The problems and limits of EA center on how it manipulate. Thus, auricular acupuncture (AA) might be a sound treatment to feather all patients’ needs for convenience and comfort. Compared with a pile of studies conducted the access to the effectiveness of EA against CINV, the role of AA has received less attention,^[18]^ and the literatures on AA are limited in number with uncertain quality.

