	(2g) Needle type (diameter, length, and manufacturer or material)	Group A: Sterile intradermal acupuncture needles (PYONEX, 0.21.2 mm, SEIRIN Corporation, Japan)Group B: Sterile single-use needles (Shukang, ϕ0.25 × 40 mm, Changchun Aikang Medical Devices Co., Ltd., China)
3. Treatment regimen	(3a) Number of treatment sessions	Three consecutive chemotherapy cycles
	(3b) Frequency and duration of treatment sessions	Once a day
4. Other components of treatment	(4a) Details of other interventions administered to the acupuncture group (e.g., moxibustion, cupping, herbs, exercises, lifestyle advice)	None
	(4b) Setting and context of treatment, including instructions to practitioners, and information and explanations to patients	The same practitioner will treat every session for 1 participant.
5. Practitioner background	(5) Description of participating acupuncturists (qualification or professional affiliation, years in acupuncture practice, other relevant experience)	Licensed Traditional Chinese medicine doctor with >5 years of acupuncture treatment experience
6. Control or comparator interventions	(6a) Rationale for the control or comparator in the context of the research question, with sources that justify this choice	No acupuncture will be performed on the control group
	(6b) Precise description of the control or comparator. If sham acupuncture or any other type of acupuncture-like control is used, provide details as for Items 1 to 3 above.	No sham acupuncture will be performed on the control group

Participants in Group A will receive the following treatment. After each insertion site be disinfected with 75% alcohol, sterile intradermal acupuncture needles (PYONEX, ϕ0.2 × 1.2 mm, SEIRIN Corporation, Japan) will be inserted vertically to a depth of 1.2 mm. Participants will be requested to put pressure on the each auricular point for about 15 seconds per one time, 3 times per day.

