### Sample size calculation

2.6

Using the frequency of onset as the primary outcome measurement, NQuery Advisor software (version 4.0, Statistical Solutions, Ireland) was used to calculate the appropriate sample size. Based on literature research, the sample size was estimated according to the calculation formula of non-inferiority test. α = 0.025, β = 0.2, non-inferiority margin δ = 15%, ε is the actual difference among groups. One-way test was performed, and the sample size was calculated to show that 103 samples are needed in this study. One hundred eighteen cases were needed in the 3 groups, assuming a 10% non-adherence to treatment and a 5% loss to follow-up. In this study, a total of 120 cases were selected from 3 groups, 40 cases in each group.

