### Statistical analysis

2.8

All continuous data will be expressed as mean ± standard deviation. For these data, a *t* test will be applied to compare normally distributed data between the 2 groups, while the Wilcoxon rank sum test applied for non-normally distributed data. Categorical variables will be presented as frequency and percentage and analyzed using the chi square (χ2) test or the Mann–Whitney *U* test where appropriate. Values of *P* < .05 (2-tailed) will be considered statistically significant. All the efficacy and safety analyses will be performed using the intent-to-treat population. All statistical analyses will be performed using the Statistical Package for the Social Sciences (version 13.0; SPSS; Chicago, IL). A third person performed blinded estimation and statistics of the curative effect.

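### The primary outcome (section 2.5.1), the endpoint used for sizing (2.6) and the planned tests (2.8) do not describe the same analysis, and judging each listed primary result at .05 inflates the false-positive rate

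*Protocol article*

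**What the plan says.** **Primary outcome (2.5.1).** Two instruments are joined as one primary outcome: "The primary outcome measure will be the definition and classification of nausea and vomiting (NCI-CTC AE4.0) and the MASCC" Antiemesis Tool (MAT). The first "stages the nausea and vomiting into 3 and 4 grades, respectively", so the two symptoms are graded separately. In the MAT, "each section has 4 identical items including occurrence of nausea and vomiting, frequency of vomiting, and level of nausea", and no total is defined. Timing is given as "Antiemesis Tool (MAT) score, 24 hours and fourth day after chemotherapy, for a third consecutive cisplatin-based chemotherapy cycle". Treatment runs over "Three consecutive chemotherapy cycles" (Table 1), so the timing phrase can mean the third cycle only or all three.

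**Sample size (2.6).** The calculation begins "Using the frequency of onset as the primary outcome measurement". It uses a non-inferiority formula with α = 0.025, β = 0.2 and a 15% margin. The true difference ε is named but given no value, and no event rate is stated. The pair of arms being compared is not named. The result is 103, raised to 118 and then to 120, or 40 per arm.

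**Analysis (2.8).** For continuous data a *t* "test will be applied to compare normally distributed data between the 2 groups", with rank tests or chi-square for other data. Any two-tailed P below .05 counts as significant. Non-inferiority is not mentioned.

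**The concern.** A reader cannot tell which result decides this trial. Section 2.5.1 offers several, 2.6 offers one that 2.5.1 does not define, and 2.8 applies the same .05 threshold to whatever is compared. Two consequences follow.

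- If each listed primary result is tested at .05, the chance that at least one is significant when nothing differs is above 5%. That result could then be reported as the primary finding.
- The result reported need not be the one the trial was sized for. The sizing supports a non-inferiority conclusion against a 15-point margin, and a difference test at two-tailed .05 does not deliver one. A non-significant difference with 40 per arm would not show that AA is within 15 points of EA.

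Section 2.7 says that participants and acupuncturists cannot be blinded, which makes it more important that the decisive endpoint be fixed in advance.

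**Working it through.** **1. The three sections side by side**

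| | 2.5.1 | 2.6 | 2.8 |
|---|---|---|---|
| Endpoint | NCI-CTC AE grades and MAT, two times, cycle(s) unclear | one quantity, not defined | none named |
| Hypothesis | none stated | non-inferiority, 15 points | difference |
| Level | none stated | α = 0.025, one-way (read as one-sided) | .05, two-tailed |
| Comparison | none stated | not named; three groups | two groups |

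**2. The plan's own figure**

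The inflation step reproduces: 10% + 5% = 15%, and 103 × 1.15 = 118.45, reported as 118. Then 120 / 3 = 40 per arm.

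The 103 itself cannot be reproduced without an event rate and ε. For proportions,

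n per arm = (1.960 + 0.842)² × [p₁(1 − p₁) + p₂(1 − p₂)] / (δ + ε)², with δ = 0.15.

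With ε = 0, a figure close to 103 arises in three ways:

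- as a three-arm total at a rate near 5% (34 per arm, 3 × 34 = 102);
- as a two-arm total near 8% (52 per arm, 2 × 52 = 104);
- per arm near 18%.

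The only background rate in the article is in the Introduction: vomiting controlled in 60% of patients on guideline drugs. Using that as an assumption, 7.849 × 2 × 0.24 / 0.0225 gives 168 per arm at ε = 0. It gives 92 per arm for a true gain of 5 points and 38 for a gain of 15. None of these calculations allows for more than one endpoint or contrast.

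**3. How many primary results 2.5.1 contains**

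- One score per instrument, one cycle: 2 instruments × 2 times = 4.
- Nausea and vomiting kept separate, one cycle: 2 × 2 × 2 = 8.
- Nausea and vomiting kept separate, three cycles: 8 × 3 = 24.
- Contrasts: AA versus EA only (1 pair), or all pairs among three arms (3).

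The MAT's four items per section could raise these counts.

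**4. Chance of at least one false positive at .05 per test**

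Model: no true differences; arm-level endpoint scores standard normal with equal correlation ρ between endpoints; pairwise contrast Z = (difference)/√2; significant if |Z| > 1.960. The pairs share arms, so their dependence is included. The correlations are assumed, since the article gives none. Simulation with 200,000 runs per cell:

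| Reading | ρ = 0.5 | ρ = 0.8 | ρ = 0.9 |
|---|---|---|---|
| 4 endpoints, AA vs EA | 16% | 11% | 9% |
| 8 endpoints, AA vs EA | 25% | 16% | 12% |
| 1 endpoint, 3 pairs | 12% | 12% | 12% |
| 8 endpoints, 3 pairs | 51% | 34% | 27% |
| 24 endpoints, 3 pairs | 77% | 47% | 34% |

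For reference, fully independent tests would give 1 − 0.95²⁴ = 70.8% for 24 tests and 1 − 0.95⁷² = 97.5% for 72. These overstate the rate here, because the measures are positively related and the arms are shared.

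**The case against.** **The analysis plan is not shown.** A multiplicity rule, a test order and endpoint detail are commonly left to it, and a journal article condenses. This stands as far as it goes: the absence of an adjustment is not in itself the point. What remains is what the article fixes. It gives several joint primaries, a different sizing endpoint, a non-inferiority sizing with a difference analysis, and one threshold for all P values. An analysis plan would still have to choose between 2.5.1 and 2.6.

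**The size depends on the reading.** A reader might infer at least 72 primary tests (24 endpoints × 3 pairs). The text does not support that as a minimum. The cycle wording may mean cycle 3 only. No section says that all three pairs will be tested, and the stated aim is AA versus EA. The two-group wording may be that one contrast, or a carry-over from a two-arm text (2.7 also speaks of two groups), and a chi-square can be run across three arms. The narrower readings give 9–25%, not 77%.

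**Non-inferiority to an ineffective EA.** The Introduction says "EA is still judged as a highly suggestive but not conclusive treatment". A reader might infer that the plan lets AA be declared non-inferior to an EA that did nothing. With both true rates at 40% and 40 per arm, a non-inferiority test at 15 points would succeed in about 28% of trials. The arithmetic is right, but 2.6 does not name AA versus EA as the non-inferiority pair, 2.8 plans no such test, and 40% is an assumed rate. Whether EA works in this trial is a separate question from multiplicity.

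**Gating has a price.** Requiring EA to beat control, then AA to beat control, then AA non-inferior to EA would place the trial's own question last. At 40 per arm, with assumed rates of 40% under control and 20% in both active arms, the first step succeeds in about 50% of trials, the first two in 33% and all three in about 14%.

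**Conclusion.** The point holds as a contradiction within the article: the primary outcome, the sizing endpoint and the planned tests do not match, and no primary contrast is named. The mismatch needs no assumption.

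The false-positive inflation is conditional on judging each joint primary result at .05, on the reading of 2.5.1 and 2.8, and on assumed correlations of 0.5 to 0.9. Every reading calculated here exceeds 5%, from about 9% at the narrowest to about 77% at the widest. The article does not settle where in that range the trial lies, and this ambiguity is part of the defect. The documents support neither a fixed count of 72 tests nor the claim that the plan would declare AA non-inferior to an ineffective EA.

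**What to change.** 1. Name one primary endpoint, giving the measure, the time window, and the cycle or summary over cycles. Define it identically in 2.5.1 and 2.6.
2. Name AA versus EA, the trial's stated question, as the primary contrast in 2.6 and 2.8.
3. Analyse that contrast in 2.8 by the method used for sizing: a one-sided 97.5% confidence bound for the difference, compared with the 15-point margin.
4. Make all other scales, times, cycles and contrasts secondary.
5. Recheck and restate the sample size or power for the chosen endpoint, with its assumed rates and ε.
6. Report EA versus control and AA versus control alongside, as supportive evidence on whether EA works in this trial. Making them formal gates is the sponsor's choice and carries the power cost shown above.

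The change is to wording and calculation; it needs no new data or visits. The cost is that the other scales, times and cycles lose primary status and that the restated power may be less favourable. For example, with 40 per arm, ε = 0 and an assumed 40% rate in both arms, power against the 15-point margin is Φ(0.15/√(2 × 0.24/40) − 1.960), or about 28%.

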#### Secondary outcome measures

2.5.2

Secondary outcome measures are as follows:

a.Abdominal distension is defined as a score of Likert-type scale at 24 hours and fourth day after chemotherapy. Scores on Likert-type scale range from 1 to 5, with a score of 5 indicating no symptoms; a score of 1 indicating severe distension, interfering sleep (Table 2).b.The time of first defecation is recorded as a relatively objective indicator to describe the digestive function of participants.c.The World Health Organization Quality of Life scale will be performed on each patient once a month, 3 times in total.

**Table 2 T2:** The Likert-type scale.

Scores	Symptoms
1	Severe distension, even interfering sleep
2	Salient distension and refuse to feed
3	Endurable distension
4	Slight distension
5	No symptom

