**Methods::**

One hundred twenty participants, 18 to 75 years old malignant tumors will receiving chemotherapy with cisplatin, will be recruited and randomized into 3 groups equally, Group A (the AA group), Group B (the EA group), and Group C (the control group). The participants in Group A and Group B will receive AA or EA regimens, alternatively, beginning on the day before first day of chemotherapy for a third consecutive cycles. All participants will continue to receive conventional treatment. The incidence and severity of CINV will be assessed using the definition and classification of nausea and vomiting (NCI-CTC AE4.0) and the MASCC (Multinational Association for Supportive Care in Cancer) Antiemesis Tool (MAT). Secondary outcome measures include the degree of abdominal distension, the first time of flatus and defecation, and life quality. Additionally, adverse events will also be documented during the period of the treatment.

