As for the participants in Group B, Shukang brand needles (size 0.25 mm × 40 mm) made by Changchun Aikang Medical Devices Co., Ltd., China, will be used to perform the acupuncture treatments. Stimulation will be applied until the patient experiences de qi (obtains qi). A patient's experience of de qi may take on multiple unique manifestations at the needle site itself and/or around the site of needle manipulation including soreness, aching, numbness, tingling, and even warmth. Electrical stimulation of acupuncture needles will be done at the frequency of 15 Hz with continuous wave in order to ensure patient comfort, lasting 30 minutes.

Participants in the above 2 groups will individually be needled for 4 days, beginning on the day before first day of chemotherapy and ending on the last day of it. The intervention will be applied for a third consecutive cycle. Only well-trained acupuncturists with >5 years of clinical experience could conduct acupuncture manipulation.

Subjects in the control group (Group C) will not receive acupuncture treatments. They will receive conventional Western medicine treatment only.

All patients undergo supervision and evaluation of curative effect at 10 am daily, until discharge. A third party will perform all data analysis. The flow chart of this trial is shown in Fig. 1.

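### Time of first defecation is a time-to-event outcome, but the plan names only mean ± SD with a t test or Wilcoxon test and gives no rule for patients without the event at discharge

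*Protocol article*

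**What the plan says.** All references are to the protocol article.

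- **Outcome (section 2.5.2, item b).** "The time of first defecation is recorded as a relatively objective indicator to describe the digestive function of participants". No time origin, end of recording or rule for a patient without the event is given. The Methods paragraph of the abstract lists "the first time of flatus and defecation", so flatus appears there as a second outcome of the same kind.
- **Analysis (section 2.8).** Continuous data are expressed as mean ± standard deviation. The t test is assigned to normal data, "while the Wilcoxon rank sum test applied for non-normally distributed data". No time-to-event method is named.
- **Population (section 2.8).** "All the efficacy and safety analyses will be performed using the intent-to-treat population".
- **Observation (section 2.4).** "All patients undergo supervision and evaluation of curative effect at 10 am daily, until discharge". The day of discharge is not given.
- **Background treatment (Introduction and section 2.4).** All three groups receive conventional antiemetics. The Introduction lists the side effects of these drug classes, "namely insomnia, headaches, dizziness, and constipation".

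**The concern.** Time of first defecation is observed only if the event happens while someone is recording it. For a patient discharged beforehand, all that is known is that the time exceeds the stay. The method that section 2.8 assigns has no place for that information: a mean and a t test need a number for every patient. An analyst following the text must drop the patient, invent a value, or depart from the plan.

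The document's own account makes such patients plausible, since every arm receives drugs for which constipation is listed as a side effect. It gives no rate, so it does not show that they will be common.

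At stake is an outcome that the protocol values for being relatively objective, in a trial where participants and practitioners are not blinded (section 2.7). If the handling of unobserved times is settled only after the data are seen, the result depends on a choice that should have been fixed beforehand.

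**Working it through.** The plan states no expected time, SD, discharge day or share without the event for this outcome, so there is no figure of its own to reproduce. The sample size in section 2.6 concerns a different outcome and plays no part here.

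**Inputs from the document:** 40 patients per arm (section 2.6); two-sided 5% tests (section 2.8); observation to discharge (section 2.4).

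**Assumptions:** mean times of 36 h and 48 h (true difference 12 h); gamma shape 1 (exponential), gamma shape 3 or lognormal (sigma 0.6) times; discharge at 72 to 240 h.

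**Step 1. One case by hand.** For exponential times with mean m, let q = exp(−T/m) be the share without the event at discharge time T. The mean among those with an observed event is m − T·q/(1 − q).

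- T = 72 h, m = 36: q = 0.135, mean = 36 − 11.27 = 24.73 h.
- T = 72 h, m = 48: q = 0.223, mean = 48 − 20.68 = 27.32 h. Difference 2.59 h instead of 12 h.
- T = 240 h: q = 0.0013 and 0.0067; means 36 − 0.31 = 35.69 h and 48 − 1.63 = 46.37 h. Difference 10.68 h.

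**Step 2. Common discharge time, patients without the event dropped (simulation, range over the three distributions).**

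| Discharge | Without event, per arm | Difference left (true 12 h) |
|---|---|---|
| 72 h | 6–22% | 2.6–5.9 h |
| 96 h | 1–13% | 4.2–8.5 h |
| 144 h | 0.1–5% | 7.0–11.3 h |
| 240 h | under 1% | 10.6–12.1 h |

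The hand results agree with the simulation to within about 0.1 h; the 12.1 is simulation noise around 12.

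**Step 3. Wilcoxon power, 40 per arm, gamma shape 3.** With full data it is 53%. With patients dropped it is 28% at 72 h, 43% at 96 h and 52% at 144 h. With the same patients kept and ranked worst it is 52–53% throughout.

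**Step 4. Discharge times that differ by arm (gamma shape 3, patients dropped).** With the faster arm discharged at 72 h and the slower at 120 h, the difference becomes 13.6 h. At 60 h versus 144 h it is 17.1 h. At 72 h versus 96 h it is 10.9 h. Both the size and the direction of the distortion depend on discharge practice.

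**Step 5. A second set of assumptions.** Take Weibull times (shape 1.5) with medians of 2 and 3 days. At a day-4 discharge the shares without the event are exp(−ln 2 × (4/2)^1.5) = 14% and exp(−ln 2 × (4/3)^1.5) = 34%. The true mean difference of about 1.15 days falls to 0.26 days among observed events. Power is about 15% for the complete-case t or Wilcoxon test, against 66% for the log-rank test. At day 7 the difference left is 0.72 days, with power of 43–49% against 75%.

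**The case against.** **Nothing says that these patients are excluded.** This is correct. Section 2.8 places all efficacy analyses in the intent-to-treat population, which sits badly with silent exclusion. But that sentence says whom to analyse, not what value an unobserved time takes, so it does not close the gap.

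**Recording may not stop at discharge.** This is also fair. Assessments on the fourth day after chemotherapy and the monthly quality-of-life contacts may fall after discharge. They are specified for nausea and vomiting, distension and quality of life, however, and none is specified for defecation.

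**The Wilcoxon test is already named and is adequate.** With patients without the event ranked worst, it loses almost no power (step 3). What is missing is the rule that makes it usable here.

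**A condensed article may leave this detail to a fuller document.** That limits the point. The missing rule alone would not be a finding. The article does, however, assign a method to all continuous data, and for this outcome the mean and t test do not fit.

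A reader might go further and infer that the slowest patients will drop out, that the difference will therefore shrink towards zero, and that most of the power will be lost. The documents do not support this. It needs a meaningful share without the event, their exclusion, and similar discharge times across arms, and none of the three is stated. A large loss of power appears only in the early-discharge scenarios; at 144 h, step 3 shows 52% against 53%. Nor is this outcome the only indicator with a claim to objectivity, since frequency of vomiting and first flatus are also recorded.

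**Conclusion.** The point holds as a conditional risk and a cheap improvement, not as a demonstrated bias. The stated mean ± SD and t test cannot use a patient who has not had the event by the last observation, and no rule says how such a patient enters the Wilcoxon test. If patients of this kind are not rare and are dropped, the comparison is distorted. Under the assumed 12 h difference and a common discharge time, what remains runs from about a fifth to a half of the true value at 72 h (2.6/12 = 0.22; 5.9/12 = 0.49) to nearly all of it at 240 h. With earlier discharge in the faster arm the difference can be overstated. Every time, distribution and discharge day behind these figures is an assumption, because the documents give none. Low-to-moderate severity: one secondary outcome, plus first flatus if it is retained.

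**What to change.** In section 2.5.2, measure the time from a fixed origin, such as the start of chemotherapy in the cycle, and state when recording ends. Record the discharge or last-observation time for every patient. State whether first flatus, which only the abstract names, is an outcome; if so, treat it in the same way.

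In section 2.8, take these times out of the general rule for continuous data. Analyse all randomised patients by Kaplan-Meier with a log-rank test (or a Cox model), censoring at the last observation those without the event. Censoring at discharge assumes that discharge is unrelated to bowel recovery. Where it may be related, use a Wilcoxon test with patients without the event ranked worst, either as the analysis or as a sensitivity analysis.

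The cost is a sentence or two of text and one recorded time per patient and cycle, with no change to sample size. The downside is that a median or hazard ratio is reported instead of a mean.

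### Quality of life: no questionnaire is fixed before treatment and only unadjusted tests are named, which gives up precision at 40 per arm

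*Protocol article*

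**What the plan says.** Section 2.5.2 of the protocol article lists quality of life as the third secondary outcome: "The World Health Organization Quality of Life scale will be performed on each patient once a month, 3 times in total". No starting point is given. Abdominal distension, in the same list, is tied to 24 hours and the fourth day after chemotherapy.

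Under section 2.4, needling in Groups A and B runs over four days, "beginning on the day before first day of chemotherapy and ending on the last day of it". A pre-treatment score would have to be taken before that. The visible text names no baseline quality-of-life score.

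Section 2.8 gives one rule for continuous variables. They are summarised by mean and standard deviation ("All continuous data will be expressed as mean ± standard deviation"). Student's method is the choice when normality holds ("test will be applied to compare normally distributed data between the 2 groups"). Otherwise a rank-based comparison, the Wilcoxon procedure, takes its place. No covariate, change score or repeated-measures model is mentioned. Section 2.6 sets the size: "a total of 120 cases were selected from 3 groups, 40 cases in each group".

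**The concern.** Section 2.3 admits ages 18 to 75, no restriction on tumour type, and any Karnofsky score above 60. Patients can therefore be expected to differ in quality of life at entry, although the article does not quantify this. A score taken before treatment would let the analysis remove that variation from the comparison.

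Either reading of the schedule leaves something unused. If the first questionnaire precedes treatment, the named tests make no use of it as a covariate, and comparing groups on that first score says nothing about treatment. If all three follow the start of treatment, adjustment is impossible, and a missed baseline cannot be collected later. What is at stake is the precision of one secondary comparison with 40 patients per arm.

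**Working it through.** **Inputs**
- Patients per arm: 120 / 3 = 40 (section 2.6).
- Two-sided significance level: 0.05 (section 2.8).
- Power: 80%, borrowed from β = 0.2 in section 2.6, which refers to frequency of onset and not to quality of life.
- Standard deviation: set to 1, so differences are in SD units.
- Correlation ρ between baseline and follow-up score: not in the documents. Assumed 0.3, 0.5 and 0.7.

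The article states no power or sample size for quality of life, so there is no figure of its own to reproduce beyond the 40 per arm.

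**Step 1: the unadjusted comparison**
- Detectable difference = (1.960 + 0.842) × √(2/40) = 2.802 × 0.2236 = 0.63 SD.
- Power for an assumed difference of 0.5 SD: 0.5 / 0.2236 − 1.960 = 0.276, and Φ(0.276) = 61% (60% with the exact t distribution).

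**Step 2: adjusting for baseline by ANCOVA**

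The variance is multiplied by 1 − ρ². The equivalent unadjusted number per arm is 40 / (1 − ρ²), and the detectable difference is 0.626 × √(1 − ρ²).

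| Assumed ρ | 1 − ρ² | Variance reduction | Equivalent n per arm | Detectable difference | Power for 0.5 SD |
|---|---|---|---|---|---|
| 0.3 | 0.91 | 9% | 44 | 0.60 SD | 65% |
| 0.5 | 0.75 | 25% | 53 | 0.54 SD | 73% |
| 0.7 | 0.51 | 49% | 78 | 0.45 SD | 88% |

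The percentage reductions do not depend on the number analysed. If both allowances in section 2.6 (10% and 5%) were lost from the analysis, 40 × 0.85 = 34 per arm would remain. The detectable difference would then be 0.68 SD unadjusted and 0.59 SD at ρ = 0.5.

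**Step 3: if the t test were applied to change from baseline**

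Section 2.8 does not rule this out. With equal variances at both times, a change score has relative variance 2(1 − ρ): 1.40, 1.00 and 0.60 for ρ = 0.3, 0.5 and 0.7. ANCOVA gives 0.91, 0.75 and 0.51, so it is more precise than the raw score or the change score at each of these values.

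**Step 4: what it costs to turn one of the three scores into a baseline**

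Suppose all pairs of scores correlate at ρ and the follow-up scores are averaged. The relative variances are:

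| Assumed ρ | Three follow-ups, no baseline: (1 + 2ρ)/3 | Baseline + two follow-ups: (1 + ρ)/2 − ρ² | Baseline + three follow-ups: (1 + 2ρ)/3 − ρ² |
|---|---|---|---|
| 0.3 | 0.53 | 0.56 | 0.44 |
| 0.5 | 0.67 | 0.50 | 0.42 |
| 0.7 | 0.80 | 0.36 | 0.31 |

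If the analysis averages over time, giving up a follow-up for a baseline brings nothing at ρ = 0.3 and a clear gain at 0.5 and above. Adding a fourth questionnaire helps at all three values.

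**The case against.** The strongest objection is that this is a condensed article. Which of three questionnaires is the baseline, the visit windows and covariates for a secondary outcome are commonly left to a fuller document, and the flow chart in Figure 1 is not available here. That disposes of any complaint about scheduling detail alone. It does not dispose of the analysis point, because section 2.8 positively names unadjusted tests for continuous data.

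Four stronger readings are tempting, and the documents do not support them.
- A reader might infer that no baseline is measured. The text is silent, and the first of the three questionnaires may be one.
- A reader might infer that raw scores are compared. Section 2.8 does not say so, and a t test on change scores would fit its wording. Step 3 shows that ANCOVA is still more precise.
- A reader might infer that imbalance at entry biases the result. Allocation is random, so chance imbalance is already reflected in the standard error and the unadjusted test keeps its type I error rate.
- A reader might infer that the monthly schedule clashes with the chemotherapy cycles. Cycle length is not stated, and three questionnaires could match three cycles.

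It also stands that the size of the gain rests wholly on an assumed correlation and is small at 0.3. No primary conclusion depends on this outcome.

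**Conclusion.** The point holds as a minor improvement in precision. The article leaves open whether a quality-of-life score is taken before treatment, and the tests it names would not adjust for one. The unadjusted comparison is valid but less efficient. The gain forgone is a variance reduction of 9%, 25% or 49% at assumed correlations of 0.3, 0.5 or 0.7, equal to about 44, 53 or 78 patients per arm instead of 40. This assumes a linear relation between baseline and follow-up, equal variances across arms, and 40 analysed per arm for the equivalent numbers. Neither bias nor an invalid test follows from the text.

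**What to change.** In section 2.5.2, state that the first questionnaire is completed before cycle 1 treatment begins, and at the same time point relative to chemotherapy in Group C, which has no needling to anchor it. State when the later questionnaires are given.

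In section 2.8, state that groups are compared on the later quality-of-life scores by ANCOVA, or by a repeated-measures model, with the baseline score as covariate.

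The cost is wording plus one extra questionnaire per patient. If the total stays at three and none is already taken before treatment, one follow-up score becomes the baseline, with the trade-off shown in Step 4. If the first is already a pre-treatment score, only the wording and the analysis change. It should be confirmed that Group C patients are seen before chemotherapy, since the article describes a visit on the preceding day only for the two needled groups.
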